#### Other outcomes analyses

We will assess internal consistency of the MMAS-8 scale in our trial population by Cronbach’s alpha coefficient and reliability of the summed score by McDonald’s hierarchical omega, which has been shown to be a superior measure to Cronbach’s alpha [97]. We will also provide the measures of sensitivity and specificity of MMAS-8 related to correct prediction of high blood pressure. Of interest is also the relationship between two measures of adherence (MMAS-8 and pill count), which will be analyzed using correlation coefficients (Pearson and Kendall tau). Additionally, regression techniques to analyze the impact of co-variables, such as: age, gender, education level, social status, place of residence, number of daily doses, co-medication, co-morbidities (concomitant diseases, smoking status), and pharmacy on patients’ adherence will be applied.

Since we are interested in providing relevant information for the decision-making process, we will conduct a simple cost-effectiveness analysis. Here, we will focus only on the differential costs that depend on the choice of alternative care (usual pharmaceutical care or SMS reminder).

Finally, we will collect, report, and perform a qualitative analysis of the refusal to participation in the trial and withdrawal from the trial rates.

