### Outcome measures

#### Primary outcome measure

Our primary outcome is the proportion of adherent patients in the intervention group after three months of receiving SMS reminders of medication intake. For these purposes, we will assess patients’ adherence via combined adherence endpoint consisting of self-reported medication adherence measured via MMAS-8 and pill count rate (%).

The eight-item MMAS questionnaire, on which the MMAS-8 is based, evaluated hypertensive patients. It showed good reliability (α = 0.83) as well as sensitivity (93%) and specificity (53%) in the identification of lower versus higher adherence to antihypertensive medication. Additionally, the association between MMAS-8 and blood pressure control was proved statistically significant (*p* < 0.05) [19]. Each question aims at assessing a specific medication-taking behavior, either intentional or unintentional. The first seven questions have dichotomous answers (yes/no), whereas the last question offers a five-point Likert response. The range of the scores is from 0 to 8 with 0 being low adherence and 8 indicating full medication adherence [19, 74].

Pill count is a simple objective indirect measurement of patients’ adherence to medication intake [75]. AR will be calculated using the following equation:$$ \mathrm{A}\mathrm{R}\left(\%\right)=\left(\frac{\mathrm{No}.\mathrm{of}\;\mathrm{pills}\;\mathrm{actually}\;\mathrm{taken}}{\mathrm{No}.\mathrm{of}\;\mathrm{pills}\;\mathrm{that}\;\mathrm{should}\;\mathrm{have}\;\mathrm{been}\;\mathrm{taken}}\right)\times 100 $$

No specific guidelines exist on how to assess medication adherence [76]; therefore, we based our categorization of a patient as being “adherent” or “non-adherent” on the previous literature and expert opinions. Our study team agreed that a patient at the end of the trial will be considered as either “adherent,” having MMAS-8 ≥ 6 [19] and pill count rate ≥ 80% [77], or “non-adherent” if one or both of the previous conditions are not met. Table 3 contains details on our primary outcome measure.

**Table 3 Tab3:** Primary outcome Combined adherence endpoint

Level	
Domain	Combined medication adherence
Specific measurement variable	Adherence status (dichotomous) adherent: MMAS-8 score ≥6 and pill count rate ≥80% non-adherent: MMAS-8 score <6 and/or pill count rate <80%
Analysis Metric	Final value (Visit 2)
Method of aggregation	Proportion of adherent patients (%)

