#### Patients’ satisfaction with SMS reminders

First, we will analyze the psychometric quality of the questionnaire items. Cronbach’s alpha, McDonalds’s hierarchical omega, as well as Mokken scale analysis [95] will be used to find out if all items have sufficient quality to be included in the final scale. In case of significant deficiencies, item(s) will be excluded. Second, using the final scale, we will analyze the impact of patient satisfaction level on the change of adherence and systolic blood pressure values via multivariate linear regression, controlling for impact of sex, age, education, etc. This way we strive to find out if the overall satisfaction level of patients is a significant predictor variable for the change in ARs and/or systolic blood pressure values.

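### The plan labels hierarchical omega as the reliability of the MMAS-8 summed score; the two agree only if the scale has no group factors, so the reported reliability may be too low

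*Protocol article*

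**What the plan says.** Under Other outcomes analyses, the protocol article gives two coefficients separate jobs. On the first it says: "We will assess internal consistency of the MMAS-8 scale in our trial population by Cronbach’s alpha coefficient". The second is to give the "reliability of the summed score by McDonald’s hierarchical omega", and the article calls this measure better than alpha. Omega total is not named anywhere in the article.

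The section Primary outcome measure describes the instrument: "Each question aims at assessing a specific medication-taking behavior, either intentional or unintentional". On item format it says: "The first seven questions have dichotomous answers (yes/no), whereas the last question offers a five-point Likert response". The items are used as one score from 0 to 8, cut at 6 for the combined endpoint, and an alpha of 0.83 is cited from earlier work. No factor structure, item grouping or loadings are given.

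Hierarchical omega appears again under Patients' satisfaction with SMS reminders. There, together with Cronbach's alpha and Mokken scale analysis, it "will be used to find out if all items have sufficient quality to be included in the final scale".

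**The concern.** Under a common-factor model, the reliability of a summed score is the proportion of its variance due to all common factors. Hierarchical omega counts only the general factor and leaves group-factor variance with the error. It answers a different question: how far the sum reflects one single construct. Calling it the reliability of the sum is therefore correct only in a special case.

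The protocol gives some reason to doubt that special case. Besides describing the items as intentional or unintentional, its Background gives the two kinds of non-adherence different causes, and its Discussion says the reminders address only forgetting.

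What is at stake is a reported psychometric result. Evaluating the MMAS-8 in this population is listed under Trial objectives, and the Discussion promises its reliability as an output. With uncorrelated errors, alpha is a lower bound on reliability. The trial could then publish, as the better reliability estimate, a figure below the alpha printed next to it.

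**Working it through.** The plan states no value for either omega, so there is no figure to reproduce. The check has two parts: the definitions, and an illustration of size.

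**Definitions (bifactor model).** Let V be the variance of the total score.

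- Hierarchical omega: ω_h = (sum of general loadings)² / V
- Omega total: ω_t = [(sum of general loadings)² + Σ over groups of (sum of group loadings)²] / V

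So ω_h ≤ ω_t, with equality only if group-factor variance is zero.

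**Inputs from the protocol.** There are 8 items, and the cited alpha is 0.83.

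**Assumptions not in the protocol.** Items are standardised and follow a linear factor model. There are two groups of four items. All within-group correlations equal r_w and all between-group correlations equal r_b, with a chosen ratio r_b/r_w. Seven of the eight real items are yes/no, so actual values would differ.

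**Step 1: mean inter-item correlation implied by alpha.** r = 0.83 / (8 − 7 × 0.83) = 0.83 / 2.19 = 0.379.

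**Step 2: total variance.** V = 8 + 56 × 0.379 = 29.22, the same for every ratio because alpha is held fixed.

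**Step 3: split the correlation.** There are 12 within-group and 16 between-group pairs, 28 in all. So r_w = 28 × 0.379 / (12 + 16 × ratio), and r_b = ratio × r_w. Each squared general loading is r_b and each squared group loading is r_w − r_b. Hence ω_h = 64 r_b / V and ω_t = [64 r_b + 32 (r_w − r_b)] / V.

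**Step 4: results.**

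| r_b/r_w | r_w | r_b | ω_h | ω_t | Gap |
|---|---|---|---|---|---|
| 1 | 0.379 | 0.379 | 0.830 | 0.830 | 0 |
| 0.9 | 0.402 | 0.362 | 0.792 | 0.836 | 0.04 |
| 0.75 | 0.442 | 0.332 | 0.726 | 0.847 | 0.12 |
| 0.5 | 0.531 | 0.265 | 0.581 | 0.872 | 0.29 |

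Worked line for ratio 0.75: r_w = 10.61 / 24 = 0.442 and r_b = 0.332. Then ω_h = 21.22 / 29.22 = 0.726 and ω_t = (21.22 + 3.54) / 29.22 = 0.847.

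**Sensitivity to the split.** At ratio 0.75, a 5/3 split gives 0.719 against 0.846 (gap 0.13), and a 6/2 split gives 0.697 against 0.842 (gap 0.15 after rounding, 0.842 − 0.697 = 0.145).

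**Sensitivity to fixing alpha.** Take instead general loadings of 0.5 and group loadings of 0.4, split 4/4. The general part is (8 × 0.5)² = 16, the group part 2 × (4 × 0.4)² = 5.12, and the unique part 8 × (1 − 0.25 − 0.16) = 4.72, so V = 25.84. Then ω_h = 16 / 25.84 = 0.619 and ω_t = 21.12 / 25.84 = 0.817, a gap of 0.20.

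**The case against.** The strongest reply is that the protocol describes what the items ask about, not how they correlate. Items on intentional and unintentional behaviour may still behave as one dimension, and then the two coefficients coincide. This stands. A reader might infer that reliability will be understated, but the documents show no group-factor variance, so only a conditional statement is supported.

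Hierarchical omega also suits the way the score is used. The MMAS-8 enters as a single adherence score, and how far that sum reflects one construct is a fair question. This stands too, and it is why the coefficient should be kept. It does not justify calling it the reliability of the sum. The protocol cites a source for preferring it to alpha, which cannot be checked here.

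Three further inferences are tempting and are not supported:

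- **That the result cannot be compared with the cited 0.83.** The same sentence of the plan also calls for Cronbach's alpha in the trial population, which gives a like-for-like comparison.
- **That sound satisfaction items will be dropped.** Alpha and Mokken analysis are used as well, nothing says hierarchical omega alone decides, and no multidimensionality of that questionnaire is documented.
- **That the primary endpoint is affected because the MMAS-8 is one of its two components.** The coefficient does not enter the cut at 6, the chi-square test, the sample size or any secondary treatment comparison.

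Nor is this merely detail left to an analysis plan: the article itself pairs a named coefficient with a quantity that it does not in general estimate.

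**Conclusion.** The point holds in a limited form. The label is wrong in general, and it is harmless only if the MMAS-8 has no group factors. Whether the reported reliability will in fact be too low is open. The gap is zero under unidimensionality and about 0.04 if the two kinds of item are nearly one dimension. It reaches 0.12 to 0.29 at correlation ratios of 0.75 to 0.5. Those sizes rest on the assumed split, the equal correlations and alpha held at 0.83; none can be derived from the protocol beyond the 8 items and the cited alpha. The matter is minor and confined to the psychometric reporting.

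**What to change.** - **Other outcomes analyses:** name omega total, with a confidence interval, as the reliability of the MMAS-8 summed score. Keep hierarchical omega beside it, labelled as general-factor saturation. Alpha stays as planned.
- **Patients' satisfaction with SMS reminders:** add omega total to the coefficients listed, and state that no item will be excluded on hierarchical omega alone.

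The cost is a few words in two sections. Both omegas come from the same fitted factor model, so no new data or analysis stage is needed. The sample size and the treatment comparisons stay as they are.

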## Discussion

The SPPA trial protocol was designed to answer the research question whether personalized daily SMS reminders of antihypertensive medication intake, provided by pharmacists in addition to sPhC, increase the proportion of adherent older hypertensive ambulatory patients.

We aimed to develop a pragmatic trial that is not only able to prove the effectiveness of SMS reminders in improving patients’ adherence to medication intake in specific trial conditions, but can be easily implemented in daily practice after end of the trial. For this purpose, we have extensively used the innovative PRECIS-2 tool [64] thorough the whole trial design period. SPPA trial scored high in most of the trial domains (Additional file 2).

Studies have shown the potential efficacy of SMS reminders in improving adherence to medications as well as health outcomes in patients with infections and chronic diseases. Now, it is necessary to investigate the effect of SMS reminders in specific communities and populations [69, 84]. Our trial addresses these needs focusing on older patients within a community pharmacy setting. Prevalence of hypertension as well as the overall cardiovascular risk increases sharply with age while drug regimens become more complex. Thus, older patients are at higher risk of unintentional adherence, which is the leading cause of non-adherence among Slovak patients [98]. Consequently, older hypertensive patients are at higher risk for uncontrolled blood pressure due to non-adherence to medication treatment and could significantly benefit from this mHealth service.

We have decided to deliver the intervention, SMS reminders of medication intake, via publicly accessible online software that is easy to operate, its use is not limited for the current trial, and it is financially affordable also in low-resource settings.

Even though in the current trial SMS reminders will be sent out centrally by the external unblinded trial pharmacist, the operation of the system is intuitive and does not require extensive training of the pharmacists. We have agreed on central SMS sending to enable blinding of the trial pharmacists (assessors) to patient allocation.

Recent development in mHeath technologies has shown their effectiveness in addressing complex health issues. However, Slovakia, like many other countries, is characterized by shortage of healthcare professionals. Therefore, physicians or nurses have limited time capacities for implementation of mHealth technologies in healthcare. Simultaneously, pharmacists are highly trained healthcare professionals that are currently redefining their professional position in healthcare, mostly due to the industrialization of pharmacy. As a result, the importance of patient-centered pharmaceutical care [53] is dynamically growing. Pharmacists are considered to be experts on pharmaceuticals and patient consultation on medicinal therapy management. Also, pharmacists are already obliged by the international guidelines [54] as well as the Slovak legislation [67, 68] to provide patients with all necessary information on medication to ensure their safe and efficacious treatment. Additionally, pharmacists are the last healthcare professionals that patients consult in the drug chain process. Thus, we believe that pharmacists have the ideal predisposition and capacities to provide certain mHealth services, such as SMS reminders of medication intake, as a part of their daily practice. In order to strengthen the pragmatic design and implementation into daily practice, we designed the SMS reminders in the SPPA trial to mirror the structure of the dispensation information currently provided to the patients according to the Slovak regulations [67]. Consequently, the SMS reminders are aimed at improving non-adherence due to forgetfulness (unintentional), stress essential information regarding medicines, and support habit formation. We also believe that SMS reminders will strengthen the patient–pharmacist relationship, which is crucial for effective healthcare provision.

Our primary objective is to assess patients’ adherence according to the combined adherence endpoint consisting of self-reported medication adherence measured via MMAS-8 and pill count. Some researchers object that self-reported adherence questionnaires, such as the MMAS-8 used in this trial, tend to be subjectively biased [99, 100]. On the other hand, they use a highly patient-oriented approach that enables provision of feedback regarding adherence behavior and point out reasons for poor medication adherence [19]. Studies have shown that results of self-reported adherence questionnaires are correlated with the results of medication event monitoring systems. Even though medication event monitoring systems enable detailed monitoring of medication adherence, they are financially unsustainable in everyday practice and often provide also erroneous measures [101]. Pill count is an objective adherence measurement, although, if used alone it also may be biased [75]. Therefore, in the SPPA trial we combine two separate, simple adherence measurements suitable for the pragmatic design of the trial. We believe that combining two independent adherence measurements will provide a more reliable and valid outcome.

We will collect patient reported outcomes in regard to their perception of and satisfaction with the SMS reminders using a questionnaire designed by our research team. We will also analyze the psychometric properties of this satisfaction questionnaire for use in future studies.

SPPA trial will provide currently lacking up-to-date data on the adherence of older hypertensive patients in Slovakia, including evaluation of the internal consistency and reliability of the MMAS-8 questionnaire in our trial population. Additionally, we will collect and report anonymous reasons for refusal of participation in the trial as well as reasons for withdrawal from trial to guide future clinical trials to best address the needs of the patient community.

We put very high accent on documentation quality and data transparency. Accordingly, we will document all contacts between patients and research team as well as all problems and issues in form of contact reports. With our trial, we want to contribute to public research data sharing towards open science. Therefore, all anonymized data forms and contact reports will be made publicly available on the Open Science Framework platform [102].

The main limitation of the SPPA trial is that our current sample size lacks statistical power to detect significant change in clinical outcome, the systolic blood pressure. Also, the SPPA trial is not designed to focus on other important clinical outcomes such as cardiovascular risk reduction, prevention of cardiovascular events, or overall cardiovascular mortality. Furthermore, we formulate the SMS content solely to remind patients of their medication intake, not to educate or motivate them in any specific way, as some previous studies have intended [70, 84, 103]. Thus, our investigated intervention addresses only unintentional non-adherence due to forgetfulness, not intentional non-adherence. We have opted for this intervention since the majority of Slovak patients report forgetting as the major cause of non-adherence [98]. Moreover, pharmacies are highly accessible in Slovakia and at least one antihypertensive drug within each class is fully reimbursed by the public health insurance. Access to antihypertensive medicines is therefore not an obstacle for patients’ adherence in Slovakia.

Additionally, we collect patients’ health and medication information as patient-reported outcomes. Since pharmacists in Slovakia do not have access to patients’ health or medication history, patients are their only source of this information also in everyday practice. Thus, on the one hand, our pragmatic trial design reflects everyday practice; on the other hand, it also presents a limitation relying on the memory and truthfulness of the patients.

Another limitation of the study is that pill count assessment used alone, as in our secondary analysis, is often not valid. Patients may tend to remove their pills before the visit to please the healthcare provider who performs the pill count. Nevertheless, we have decided to include this outcome in our secondary analysis based on the following rationale. First, pill count as a research method is not frequently used in Slovakia and we will not explicitly inform the participants that their pills will be counted. Hence, participants will not be alerted to this fact. Second, we assume that patients’ primarily want to please their physician, who prescribed them the medicines and not necessarily the pharmacist, viewed more as a trusted counselor, in front of whom there is no need to hide information on medication intake.

The three-month intervention period is relatively short to ensure long-lasting clinical improvement and the potential benefits may wear off with time. However, once the initial clinical benefit, feasibility, patient acceptance, and cost-effectiveness are proven in this trial, we plan to conduct follow-up research to address these limitations.

A limitation to the pragmatic trial design is also that the external unblinded trial pharmacist is sending the SMS reminders centrally. We have accepted this limitation to ensure the blinding of the trial pharmacists as assessors of patients’ adherence, which is the primary objective of the current trial.

The SPPA trial will be the first registered pharmaceutical clinical trial in Slovakia. Understanding the need of evidence-based pharmaceutical care (EBPC) [57, 104], we aim at improving the quality of pharmaceutical care through EBPC also in the currently presented trial. SPPA trial addresses the main healthcare challenges not only in the Slovak Republic: high prevalence of hypertension and other secondary cardiovascular diseases, overconsumption of cardiovascular drugs, alarmingly low AR to long-term medication treatment, and high rates of uncontrolled blood pressure. In countries, whose healthcare systems lack financial resources and healthcare professionals, similar to the Slovak Republic, a simple mHealth intervention in form of SMS reminders of medication intake provided by pharmacists may be an efficient way to address all of these problems.

The SPPA trial will provide essential information to design future studies assessing mHealth technologies through EBPC. Therein, we will concentrate on clinically important outcomes, provided that the SPPA trial shows promising results in improving systolic blood pressure. The focus on objective clinical outcome will also enable directly the pharmacists to send the SMS reminders to patients without the need to remain blinded. Moreover, we will adjust the intervention to better reflect patients’ needs using the collected patient reported outcomes in the presented trial. Detailed publicly available reporting of the SPPA trial will serve as a source of valuable information on methodology, design, and conduct of pragmatic clinical trials in community pharmacies.

## Trial status

This study is currently recruiting participants.

## Abbreviations

AR: Adherence rate
CONSORT: Consolidated Standards of Reporting Trials
EBPC: Evidence-based pharmaceutical care
mERA: Guidelines for reporting of health interventions using mobile phones: mobile health (mHealth) evidence reporting and assessment
mHealth: Mobile health
MMAS-8: Eight-item Morisky Medication Adherence Scale
PRECIS-2: PRagmatic Explanatory Continuum Indicator Summary
QUINT: Qualitative INteraction Trees
SMS: Short messaging service
sPhC: Standard pharmaceutical care
SPIRIT: The Standard Protocol Items: Recommendations for Interventional Trials
WHO: World Health Organization
